#### **(IV) Expected results**

After basic periodontal treatment combined with hDP-MSC localized injection treatment, local periodontal inflammation was relieved or disappeared, and periodontal tissues were regenerated to a certain extent.

##### **1. Periodontal observation**

1-12 months after hDP-MSC localized injection treatment, compared with pre-treatment and basic periodontal treatment only, the redness and swelling of gingiva in the periodontitis area disappeared or receded, bleeding of gingiva disappeared or decreased, and the looseness of teeth was improved.

##### **2. Clinical indicators**

3-12 months after hDP-MSC localized injection treatment, compared with pre-treatment and basic periodontal treatment only, clinical examination showed that the AL, PD and BOP index at the periodontitis site were reduced.

##### **3. Imaging examination**

3-12 months after hDP-MSC localized injection treatment, compared with pre-treatment and basic periodontal treatment only, oral CBCT examination can see the hard tissue proliferation in the periodontal area of the injected teeth and the alveolar bone edge, or the volume of the periodontal hard tissue defect reduced.

#### **(V) Study design**

**1. This study is a single-center, randomized, controlled study of basic periodontal basic treatment combined with hDP-MSC localized injection, the sample size was 96 cases.**

**2. The study conducted two phases: the first phase consisted two groups randomized according to a 1:1 ratio; the second phase consisted of three groups randomized according to a 1:1:3 ratio.**

**2.1 Randomization method:** The randomization method for each stage of the study was district group randomization, and the statistician used SAS 9.4 software to generate random group codes. In phase 1, subjects were assigned to the DPSCs injection group and saline injection group, randomization envelopes were retrieved by the SAS unit upon completion of this phase; Phase II subjects were assigned to the single DPSCs injection group, double DPSCs injection group and the saline injection control group in the ratio of 1:1:3 according to the code of this phase.

**2.2 Inclusion Criteria:** Subjects must meet all of the following criteria to be included:

- (1) Age 18-65 years old, gender is not limited;
- (2) Voluntarily participate in this clinical study and sign the informed consent form;
- (3) Radiologic detection of wedge-shaped bone defects at the periodontal defect sites;
- (4) The probing depth (PD) of the periodontal defect site was 4-8 mm.

**2.3 Exclusion Criteria: subjects meeting any of the following will be excluded:**

- (1) Hypertensive subjects with blood pressure: systolic blood pressure  $\geq 180$  mmHg or diastolic blood pressure  $\geq 110$  mmHg within 1 month prior to surgery;
- (2) Systemic diseases (subjects with malignant tumors or those who tested positive for tumors during the screening process, diabetic subjects, cardiac diseases resulting in heart failure, and myocardial infarction within six months; angina symptoms within six months; congenital heart disease);
- (3) Subjects have used non-steroidal anti-inflammatory drugs, steroidal hormone therapy within three months prior to surgery, and/or those who have used hormones for a long period of time, those who have used bisphosphonates;
- (4) Systemic infections;
- (5) Subjects have undergone surgical treatment of periodontal defect sites and adjacent periodontal tissues;
- (6) Subjects who are known to be allergic to any materials used in the surgical procedure; (allergy, history of allergy to blood products;)
- (7) Severe periodontitis (alveolar bone resorption exceeding 2/3 of the length of root);
- (8) Subjects with severe hepatic and renal insufficiency;
- (9) Subjects with bleeding tendency or coagulation disorders ( $WBC < 3.0 \times 10^9 / L$  or  $PLT < 60 \times 10^9 / L$ );
- (10) HIV or hepatitis B virus infection;
- (11) Subjects had unprotected sex within one month prior to study screening;
- (12) Women who are pregnant, lactating, or applying estrogen for contraception;
- (13) Subjects whose own or spouses plan to become pregnant during the study and within 6 months of study completion;
- (14) Smokers (currently  $> 10$  cigarettes/day);
- (15) Subjects with an expected survival of less than 12 months;
- (16) Other circumstances deemed inappropriate for participation by the investigator.

**2.4 Withdrawal/Discharge Criteria:**

- (1) Subject has experienced adverse event during the course of the study that, in the opinion of the investigator, precludes continuation of the study;
- (2) Subjects have poor compliance and are unable to complete follow-up visits on time;
- (3) Use of other medications that affect tolerability or safety judgment, such as glucocorticoids, bisphosphonates, estrogens;
- (4) Use of other foods that affect tolerability or safety judgment, such as betel nut, or

tough foods that require prolonged chewing, resulting in bite force burden, such as beefsteak;

- (5) Subjects who wish to withdraw from the clinical study and request to investigator;
- (6) Female subjects become pregnant during the study;
- (7) Drop-out.

**2.5 Subgroup design:** The study conducted 2 phases, 96 subjects were recruited.

In phase I, there were 2 groups and 46 subjects were enrolled. After the subjects with a clinical diagnosis of chronic moderate periodontitis signed an informed consent form and met the inclusion criteria while did not meet the exclusion criteria, the investigator randomly assigned them to DPSCs injection group, approximately 23 subjects; saline injection group, approximately 23 subjects, based on the randomization grouping codes provided by the statistician. The randomization envelopes were collected by the Numerical Statistics Unit upon completion of this phase. The investigator selected the proposed treatment sites for the subjects (individual tooth site/subject). All subjects were treated with periodontal basic therapy and perform bilateral multi-point inject hDP-MSC/saline injection immediately after the completion of periodontal basic therapy.

In phase II, there were 3 groups and 50 subjects. After the subjects with a clinical diagnosis of chronic moderate periodontitis signed an informed consent form and met the inclusion criteria while did not meet the exclusion criteria, the investigator randomly assigned them to saline injection group, approximately 30 subjects; Single DPSCs injection group, approximately 10 subjects; Double DPSCs injection group, approximately 10 subjects, based on the randomization grouping codes provided by the statistician. The randomization envelopes were collected by the Numerical Statistics Unit upon completion of this phase. The investigator selected the proposed treatment sites for the subjects (individual tooth site/subject). All subjects were treated with periodontal basic therapy and perform bilateral multi-point inject hDP-MSC/saline immediately after the completion of periodontal basic therapy. At the end of the one-month follow-up, double DPSCs injection group received a bilateral multi-point inject hDP-MSC/saline.

In summary, the two phases of this study, saline group is expected to enroll approximately 33 subjects, single DPSCs injection group is expected to enroll approximately 33 subjects, and double DPSCs injection group is expected to enroll 30 subjects, which meets the requirements of statistical analysis.

### **3. blinding setup:**

This was an open study and blinded to periodontal data collectors and imaging data measurers. Since the study used DPSCs preparation had the appearance of pale creamy white homogeneous suspension after re-mixing before use, and the saline had appearance of a colorless appearance, it was impossible to blind the subjects and the investigators of local injection manipulation.

### **4. Study steps:**

#### **(1) Screening Period (D-14~0):**

**【Signed Informed Consent Form】** : The investigator fully informs the subjects about the details of the study, the treatment options for chronic moderate periodontitis, possible risks and benefits. After obtaining a written, voluntarily signed informed consent form from the subject, the subject was included in the subjects screening.

**【Inclusion/exclusion criteria】** : Screening of subjects who meet the inclusion criteria and do not meet the exclusion criteria.

**【Demographic information】** : Demographic information of the subjects will be collected and recorded, including gender, date of birth, ethnicity, height, and weight.

**【Medical history】 :** Collect and record the subject's current medical history, allergy history, family history, antecedent history (smoking, diabetes, other surgical history, etc.).

**【Vital signs】 :** respiration, heart rate, blood pressure (systolic and diastolic), temperature (axillary), and clinical assessment of general condition.

**【Periodontal Clinical Indicators】 :** Periodontal examination was standardized using the Florida Probe of the Beijing Stomatological Hospital, Capital Medical University. Records: periodontal attachment level AL, periodontal probing depth PD, probing bleeding index BOP, gingival recession GR, tooth mobility TM, and the proposed treatment site (single tooth/subject) were selected by the investigator.

**【Lab Tests】 :**

☞ Blood routine: leukocytes, erythrocytes, hemoglobin, erythrocyte pressure product, mean erythrocyte volume, mean hemoglobin volume, mean hemoglobin concentration, platelet count, mean platelet volume, platelet pressure product, neutrophils, lymphocytes, monocytes, eosinophils, basophils, neutrophil absolute value, lymphocyte absolute value, monocyte absolute value, eosinophil absolute value, basophil absolute value, erythrocyte distribution width SD, erythrocyte distribution width CV, large platelet ratio, platelet distribution width.

☞ Hemorrhagic and coagulation function: plasma prothrombin time, international normalized ratio of prothrombin time, activated partial thromboplastin time, prothrombin time, plasma fibrinogen.

☞ Liver and kidney function: alanine aminotransferase, aspartate aminotransferase, total protein, albumin, globulin, albumin-globulin ratio, total bilirubin, direct bilirubin, indirect bilirubin, alkaline phosphatase, creatinine,  $\gamma$ -glutamine acyltransferase, lactate dehydrogenase, creatine kinase, urea, uric acid, total carbon dioxide, glucose.

☞ Inflammatory markers: ultrasensitive C-reactive protein.

☞ Infectious disease tests: HBsAg, HBsAb, HBeAg, HBeAb, HBcAb, Anti-HCV, HIVcombin, Anti-TP, CMV-IgM, CMV-IgG.

☞ Immunologic tests: IgA, IgG, IgM, total IgE.

☞ Pregnancy test: blood beta-HCG, premenopausal female subjects only.

☞ Urine routine: pH, specific gravity, protein, ketone bodies, bilirubin, urobilinogen, nitrites, leukocytes, erythrocytes, urine sugar, urine sediment microscopy.

**【Basic periodontal treatment】 :** All groups of subjects underwent ultrasonic supragingival cleaning, subgingival scraping of half of the mouth and root planing. Periodontal irritants such as plaque were removed. Periodontal basic treatment required the preservation of residual dentin on the root surface according to basic principles. The investigators recorded the start and end times of the subjects' periodontal basic treatments.

■ Supragingival cleaning (D-14): saline rinsing, full-mouth ultrasonic supragingival cleaning and polishing, and saline rinsing;

■ Subgingival scaling (D-7 $\pm$ 1, non-treated tooth site area): 2% Articaine Hydrochloride anesthesia, half-mouth ultrasonic subgingival scaling, root planning, polishing and physiological saline rinse.

**【Imaging】 :** CBCT examination. The investigator re-established the treatment site of the subject (single tooth/subject).

**【Adverse Event Record】**

**【Record of combined medications/treatments】**

**【Intraoral photography】 :** Photographs were taken to record the condition of the oral cavity and treatment sites.

**【Randomized grouping】 :** Before D-2, for subjects who met the enrollment criteria, the investigators gave subjects a randomized grouping number based on the randomized grouping

code provided by the statistician to determine the group of subjects and to select the proposed treatment site.

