| Research procedure | 
(1) Screening for inclusion (D-14) : After the subjects signed the informed consent, all pre-enrollment screening examinations were conducted in the periodontal/emergency comprehensive clinic of the research institution. Subjects who met the inclusion criteria and did not meet the exclusion criteria were selected Join the group. The investigator selected the subject's proposed treatment site (single tooth position/subject).
 
(2)Periodontal primary treatment (D-14~D1) : Periodontal primary treatment includes supragingival scaling, subgingival scaling and root treatment The surface is flat. Divided into 3 times, the specific treatment steps are as follows:
 
 
■ Supragingival cleaning (D- 14) : normal saline rinse and gargle, whole mouth ultrasonic supragingival cleaning and polishing, normal saline rinse;
 
■ Subgingival scaling (D-7±1, non-therapeutic dental area) : 2% bilan anesthesia, half-mouth ultrasonic subgingival scaling, flat root surface, polishing, normal saline rinse;
 
■ Subgingival scaling (D1, including treatment area) : 2% bilan anesthesia, the other half of the mouth ultrasound subgingival scaling, root surface flat, polishing, normal saline rinse.
 
 
(3) Local injection therapy (D1) : According to the randomly assigned number, all subjects were given bilateral multi-point local injection therapy of hDP-MSC cells/normal saline immediately after the peridental foundation treatment was completed. The local injection method for the peridental defect site is: Under local anesthesia, the periodontal probe was used to determine the top position of the alveolar ridge, and the needle was injected into the bottom of the periodontal bag (in the surrounding tissue at the bottom of the periodontal bag). After the needle reached the medial periodontal membrane of the alveolar ridge and touched the junction between the bone surface and the tooth root, the multi-point interstitial injection was performed on both sides of the buccal (lip) and lingual and palatine sides with a 1ml spiral syringe. The injection time is 20-30 seconds at each point. The stop point of the injection needle is located on the tooth root surface to ensure that the injected stem cell preparation can be in the tooth root The area is clustered. Specific operations are as follows:
 
 
■ DPSCs injection group: 48 subjects. Immediately after the completion of periodontal basic treatment, the patient was given bilateral multi-point injection at a single dental position, and the therapeutic dose was <math>1 \times 10^7</math> hDP-MSC cells (0.6mL suspension of normal saline)/dental position/person.
 
■ Saline iniecton group: 48 subjects. Immediately after the completion of periodontal basic treatment, the patient was given bilateral multi-point injection at a single dental position, and the therapeutic dose was 0.6mL normal saline/dental position/person.
 
 
Local stem cell secondary injection therapy (D30±3) : Only for secondary stem cells in the second phase of this study Subjects in the administration group. At the end of a one-month follow-up, the subjects were given more hDP-MSC cells on both sides Point local injection therapy. The local injection method of periodontal defect site is the same as the first local injection treatment:
 
 
■ Double DPSCs iniecton group: After 1 month follow-up, the subjects received bilateral multi-point injection at a single dental position and the therapeutic dose It was <math>1 \times 10^7</math> HDP-MSC cells (saline 0.6mL suspension)/dental position/person.
 
 
(4) Observation (D1) : After treatment, all subjects were admitted to the periodontal/emergency comprehensive clinic 2 Hours of adverse reactions observation and safety assessment.
 
(5) Follow-up (D7±1 telephone follow-up, D30±3, D90±3, D180±5, D360±5) :
 
 
■ Post-treatment follow-up: Subjects were followed up at D7±1 (telephone follow-up), D30±3, D90±3, and D180±5 once each after discharge, and clinical safety and efficacy indexes were collected.
 
■ Long-term follow-up: After the end of treatment, D360±5 follow-up was conducted once, clinical efficacy and immunological evaluation indicators were collected, and the study was ended.
 
 |

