**(2) Baseline/treatment period (D1):**

**【Inclusion/Exclusion Criteria】** : For subjects who met the enrollment criteria, the investigators informed the subjects of the treatment tooth position information.

**【Vital signs】** : respiration, heart rate, blood pressure (systolic and diastolic), temperature (axillary), and clinical assessment of general condition.

**【Periodontal Clinical Indicators】** : Periodontal examination was standardized using the Florida Probe of the Beijing Stomatological Hospital, Capital Medical University. Records: periodontal attachment level AL, periodontal probing depth PD, probing bleeding index BOP, gingival recession GR, tooth mobility TM, and the proposed treatment site (single tooth/subject) were selected by the investigator.

**【Lab Tests】** :

☞ Blood routine: leukocytes, erythrocytes, hemoglobin, erythrocyte pressure product, mean erythrocyte volume, mean hemoglobin volume, mean hemoglobin concentration, platelet count, mean platelet volume, platelet pressure product, neutrophils, lymphocytes, monocytes, eosinophils, basophils, neutrophil absolute value, lymphocyte absolute value, monocyte absolute value, eosinophil absolute value, basophil absolute value, erythrocyte distribution width SD, erythrocyte distribution width CV, large platelet ratio, platelet distribution width.

☞ Hemorrhagic and coagulation function: plasma prothrombin time, international normalized ratio of prothrombin time, activated partial thromboplastin time, prothrombin time, plasma fibrinogen.

☞ Liver and kidney function: alanine aminotransferase, aspartate aminotransferase, total protein, albumin, globulin, albumin-globulin ratio, total bilirubin, direct bilirubin, indirect bilirubin, alkaline phosphatase, creatinine,  $\gamma$ -glutamine acyltransferase, lactate dehydrogenase, creatine kinase, urea, uric acid, total carbon dioxide, glucose.

☞ Inflammatory markers: ultrasensitive C-reactive protein.

☞ Infectious disease tests: HBsAg, HBsAb, HBeAg, HBeAb, HBcAb, Anti-HCV, HIVcombin, Anti-TP, CMV-IgM, CMV-IgG.

☞ Immunologic tests: IgA, IgG, IgM, total IgE.

☞ Pregnancy test: blood beta-HCG, premenopausal female subjects only.

☞ Urine routine: pH, specific gravity, protein, ketone bodies, bilirubin, urobilinogen, nitrites, leukocytes, erythrocytes, urine sugar, urine sediment microscopy.

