**4. verification of inclusion and exclusion criteria:** The researchers screen subjects who meet the inclusion criteria and do not meet the exclusion criteria. Comprehensive assessments are conducted for the enrolled subjects to verify if they meet all the screening and inclusion criteria.

**5. allocation of treatment/randomization numbers:** Once the researchers confirm that the subjects meet all the inclusion criteria during the screening period, they will allocate randomization numbers to the subjects based on the randomization codes provided by the statisticians. This random allocation determines the group assignment for each subject. During the baseline/treatment period, the researchers will once again confirm that the subjects meet all the inclusion criteria and inform them of their final group assignment for enrollment.

**6. study compliance management:** Once subjects receive their randomization numbers and are assigned to the researchers involved in this study, it becomes the responsibility of the researchers to track and follow up with the subjects. The researchers should diligently adhere to the study protocol and informed consent form, ensuring that the subjects fully understand the study requirements and cooperate with the research. They should also regularly remind the subjects of scheduled follow-up appointments through phone calls.

**7. compensation and reimbursement:** Subjects participating in this study will receive a fee of 300 RMB per visit as compensation for transportation expenses and loss of income. The researchers are responsible for providing this compensation in cash to the subjects at the end of each visit. If the subjects are able to complete all the scheduled visits for the study, they will receive a total of 7 compensation payments, amounting to 2100 RMB per subject.

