### **2. Statistical analysis**

The statistical analysts of this study were not involved in the screening, inclusion of subjects and subsequent clinical studies. During the course of the study, only blinded to the statistical analysts.

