## **(XX) Follow up plan and implementation methods**

The follow-up period of this study was 12 months, with telephone follow-up at  $D7 \pm 1$  after local injection treatment and regular follow-up at  $D30 \pm 3$ ,  $D90 \pm 3$ ,  $D180 \pm 5$ , and  $D360 \pm 5$ . The investigator should observe the subjects strictly according to the protocol, and the subjects should try to follow up regularly as requested by the investigator. During the study period, treatment and follow-up should be performed in strict accordance with the protocol, taking into account the fact that a time window of  $\pm 3$  days is allowed from 1 month after treatment with the stem cell preparation, and a time window of  $\pm 5$  days is allowed from 6 months after treatment. If a subject exceeds the window at a follow-up visit, the next follow-up visit should be recalculated based on the time of the previous visit.

The examinations required to be performed at each follow-up visit were conducted by the investigator, and the relevant examinations were conducted in the imaging department, laboratory department and other specialized departments of the research center, and timely, accurate and complete records were made of the clinical indicators, laboratory results and imaging results of each observation, and of the combination of medications, adverse events, and so on. For subjects with adverse reactions, all indicators of the screening period were followed up until they were normalized.

**1. Post-treatment follow-up 1:** Telephone follow-up 1 week ( $D7 \pm 1$  day) after the end of treatment.

- a. Record of adverse events
- b. Record of co-administration of drugs/treatment

**2. Post-treatment follow-up 2:** 1 month ( $D30 \pm 3$  days) after the end of treatment.

a. Vital signs: respiration, heart rate, blood pressure (systolic, diastolic), temperature (axillary), clinical assessment of the general body condition, and another checkup  $2h \pm 30min$  after the end of the second administration of treatment for the subjects in the secondary stem cell administration group in the second phase of this study.

b. Laboratory tests:

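### The protocol contradicts itself on when the study tooth is fixed, and nothing locks tooth or eligibility before the group is known

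*Protocol*

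**What the plan says.** One tooth per subject is treated and measured. The protocol speaks of choosing it in several places.

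- **At screening.** The scenario summary (research design, and research procedure at D-14) has the investigator choose the site once the subject qualifies. Section (V) 4 (1) does the same under periodontal indicators and re-establishes the site after CBCT. Half the mouth is then scaled a week before treatment: "Subgingival scaling (D-7±1, non-therapeutic dental area".
- **At allocation.** The last screening step reads "Before D-2, for subjects who met the enrollment criteria, the investigators gave subjects a randomized grouping number", using the "code provided by the statistician to determine the group of subjects and to select the proposed treatment site".
- **In the group design.** Section (V) 2.5, for both phases, places this sentence after random assignment: "The investigator selected the proposed treatment sites for the subjects (individual tooth site/subject".
- **At D1.** Section (V) 4 (2) repeats that "the proposed treatment site (single tooth/subject) were selected by the investigator". The same wording stands at D90, D180 and D360.

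On eligibility, section (9) item 5 assigns the random number at screening. Of the later visit at which treatment is given it says: "the researchers will once again confirm that the subjects meet all the inclusion criteria and inform them of their final group assignment for enrollment". The visit schedule also marks the eligibility criteria at D1.

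The trial is open. The scenario summary and section (V) 3 blind only the periodontal data collectors and the image measurers, and say the injecting investigator cannot be blinded.

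**The concern.** Randomisation protects only what is settled before the group is known. If the tooth can be chosen or changed afterwards by someone who knows the arm, the teeth compared may differ between arms in depth, defect shape or expected healing. The primary endpoint is attachment level at that tooth on D90, so such a difference would be mixed with the treatment effect. A blinded assessor does not help, because the bias enters through which tooth is presented for probing.

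The D1 eligibility check raises the same question about which subjects are kept. A subject removed after allocation and before injection is lost from the main analysis.

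**Working it through.** **1. Timing, side by side**

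| Step | Where | Relation to allocation |
|---|---|---|
| Site chosen | Scenario summary; (V) 4 (1), periodontal indicators | Before |
| Site re-established after CBCT | (V) 4 (1), imaging | Listed before |
| Side implied by scaling the other half, D-7±1 | Scenario summary; (V) 4 (1) | Before, if allocation follows that visit |
| Group and site named together | (V) 4 (1), randomised grouping | Same step |
| Site selected | (V) 4 (2), D1 | After |
| Eligibility re-confirmed | Visit schedule; (9) item 5 | After |

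The entries conflict. None says that the screening choice is final, and the re-establishment after CBCT shows that the first choice is provisional. No rule is given for choosing among eligible teeth.

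**2. Who knows the arm.** The number is given before D-2, and section (13) item 1 has the cells requested one day ahead. The study team therefore knows the group before D1.

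**3. How much freedom is left.** If allocation follows the D-7 scaling, a later choice is confined to the unscaled half-mouth. An allocation deadline of D-2 does not exclude allocation before D-7, and then even the side would be open.

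**4. Who stays in.** Under section (XIX) 2 (1) the full analysis set requires study drug and at least one efficacy assessment, so removal at D1 before injection means exclusion. Section (16) item 1 lets subjects who cannot be evaluated for safety be replaced, and its examples include those who do not meet the inclusion criteria.

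**5. Scale (illustration only).** Section (8) gives α = 0.05, power 0.80 and about 33, 33 and 30 subjects per group, but no values for S or δ. The total of 96 therefore cannot be rebuilt from its formula. Solved backwards for 33 per group:

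δ/S = √(2/33) × (1.960 + 0.842) = 0.69.

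The standard error of a difference between two arms of 33 is √(2/33) = 0.246 SD. Suppose no treatment effect, a baseline difference b, and a share c of it still present at D90. The two-sided rejection probability, without baseline adjustment, is

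Φ(cb/SE − 1.96) + Φ(−cb/SE − 1.96).

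| Assumed b | Assumed SD of AL | c = 1 | c = 0.5 |
|---|---|---|---|
| 0 | any | 0.05 | 0.05 |
| 0.25 SD | any | 0.17 | 0.08 |
| 0.5 mm | 1.0 mm | 0.53 | 0.17 |
| 0.5 mm | 1.5 mm | 0.27 | 0.10 |
| 0.5 mm | 2.0 mm | 0.17 | 0.08 |

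A shift of 0.25 SD is about one standard error, so a baseline table would not flag it. Values of b, c and the SD are all assumed.

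**The case against.** The strongest reply is that the tooth is in substance fixed at screening and the rest is loose wording. Much of this stands.

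- Eligibility is itself site-specific (a wedge-shaped defect with PD 4 to 8 mm), and the random number goes only to subjects already found eligible. A candidate site must therefore exist before allocation.
- At D1 the investigators tell the subject which tooth will be treated, which suggests it is already settled.
- In section (V) 2.5 the site sentence also follows the collection of envelopes at the end of the phase. The order of sentences there is not chronological and proves nothing about timing.
- The selection phrase at D1, D90, D180 and D360 is identical to the one at screening, and section (XX) describes the three follow-up examinations without it. It looks copied.

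A reader might therefore infer too much in four ways:

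- **That the investigator does choose the tooth knowing the arm, or chooses anew at D90.** The text permits the first and does not establish it. The second is most likely a copying slip.
- **That eligibility is decided afresh at D1.** The text describes a re-confirmation of criteria already met. A check before injection is reasonable; the problem is what happens to a subject who fails it.
- **That attachment level will be analysed with no baseline adjustment.** Section (15) names the D90 value, and section (XIX) names ANOVA or Kruskal-Wallis. An analysis plan that is not shown could add a covariate. It would correct only the measured baseline, not defect shape or access.
- **That a bias in millimetres can be read from the 4 to 8 mm entry range.** That range concerns PD, whereas the endpoint is PD plus gingival recession.

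What the reply does not remove is the randomisation step itself, which ties site selection to group determination, and the absence of any lock.

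**Conclusion.** The point holds as a contradiction and an open door, not as a demonstrated bias. Screening passages fix the tooth before allocation, the randomisation step and the D1 text place selection with or after it, and nothing decides between them. With an unblinded operator, tooth choice may depend on the arm, at least within the half-mouth left unscaled at D-7. The eligibility check at D1 is a second, smaller opening, because removal then takes a subject out of the full analysis set.

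Size and direction are undetermined. Shallower teeth in the cell arms would favour cells on the D90 value, while deeper teeth could favour them on change from baseline. The rates in the table show only that a shift too small to notice at baseline could matter. I rate this a cheap improvement.

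**What to change.** 1. After the screening CBCT, record the tooth and probing site on the CRF. Lock both, with the eligibility decision, before the allocation is opened.
2. Reword the randomised grouping step in section (V) 4 (1) so that it determines the group only, and reorder section (V) 2.5 so that site selection precedes assignment in both phases.
3. Delete the site-selection phrase at D1, D90, D180 and D360, and state that the locked site is measured at each of these visits.
4. Report by arm, with reasons, every randomised subject removed at D1, and keep them in the randomised set.
5. Separately, reconcile who is blinded. Section (XIX) 2 says "only blinded to the statistical analysts" and section (XX) says "The examinations required to be performed at each follow-up visit were conducted by the investigator", while the scenario summary and section (V) 3 provide blinded periodontal assessors. This is a distinct matter and does not bear on which tooth is chosen.

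The cost is wording and one CRF field. The downside is that the tooth cannot be changed after allocation.
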